#### Brief risk-reduction counseling

In our Uganda study, we showed that briefer modes of HIV risk-reduction counseling are likely to be equally effective as extended counseling and testing [74]. We adapted this briefer risk-reduction counseling method (10–23 min) by incorporating appropriate messages into the counseling that would addresses men’s masculinity concerns and gender beliefs about testing and treatment (see Table 2 for a breakdown of each session). The approach is male-friendly: services are provided to men in their social spaces and at their convenience; sessions are shorter and tailored to address their particular concerns; men do not have to wait in long queues; and all screening services are offered by male counselors.

**Table 2 Tab2:** Brief risk reduction counseling model

	Length of time (min)
*Protocol Component 1: pre-test counseling*	
1. Introduction of HIV testing to patients	1–5
First session time	Total 1–5
*Protocol Components 2–4: disclosure of HIV-negative results*	
2. Provide HIV-negative test result	1–2
3. Develop risk reduction plan	1–2
4. Discuss disclosure, discordance, and partner testing	1–2
Second session time	Total 3–6
*Protocol Components 5–7: disclosure of HIV-positive results*	
5. Provide HIV-positive test result and identify care resources	2–4
6. Discuss disclosure, discordance, and partner testing	2–4
7. Develop risk reduction plan	2–4
Second session time	Total 6–12

During the pre-test counseling session, the counselor explains the clinical and prevention benefits of testing, the right to refuse, the follow-up services that will be offered, and, in the event of a positive test result, the importance of disclosure to others who may have been exposed to HIV infection. If the patient has never tested for HIV, the counselor explains why it is important to know one’s HIV status and then offers the test.

Post-test counseling is tailored to the outcome of the test (positive/negative) and retain key messages (e.g. disclosure and partner testing, risk reduction, linkage to care, availability of care). The HIV-positive patient counseling session focuses on emotional support, HIV risk reduction, disclosure of HIV status, follow-up care available and referral, and partner notification and testing. Counseling for the HIV-negative patient focuses on HIV risk reduction, disclosure of HIV status, and partner notification and testing.

#### HIV testing

HIV testing is conducted using blood collected by finger-stick with a sterile lancet and using a serial testing algorithm for rapid testing according to 2015 South African National HIV Test Services guidelines [75]. All specimens are first tested with one assay (Test 1 or screening test) and specimens that are non-reactive are considered HIV-negative and reported as such. Any specimens that are reactive on the first assay (Test 1) are tested again using a different assay (Test 2 or confirmatory test). For specimens that are reactive on both the first and the second assays, results are reported as HIV-positive. Specimens that are reactive on the first assay but non-reactive on the second assay will receive an ELISA laboratory test and be recorded as discordant. In the case of discordant results, the individual is given the schedule of mobile HTS testing locations and asked to return in seven days [7] for their HIV results.

Participants are triaged according to their HIV test result. HIV-negative participants will have completed their visit, as they are not eligible for further study participation and, if required, referrals to relevant services are made. Study counselors will explain to HIV-positive men in the intervention communities that they are eligible for the randomization and the next phase of the study, if interested. All HIV-positive participants are asked for locator information (addresses and alternate/additional contact phone numbers) so if randomized into the PLC arm they can be contacted. Permission is obtained to call and/or text the participant to arrange and keep in contact for PLC.

#### Screening for non-communicable diseases

In order to destigmatize HIV testing for men, a variety of screening services for NCDs are provided alongside the screening for HIV. Procedures for hypertension, diabetes, obesity, and STI are explained to interested men, the relevant tests conducted, and results provided. Appropriate information on these conditions as well as follow-up referrals are made to nearby health facilities if further care is indicated.

#### Control communities

Control communities receive the current standard of care HTS services. All primary healthcare facilities in South Africa provide client-initiated counseling and testing (CICT) and provider-initiated counseling and testing (PICT). CICT involves individuals or couples/sexual partners actively seeking HIV testing and counseling at a facility that offers these services, while PICT is initiated and recommended by healthcare providers to all clients attending healthcare facilities as a standard component of medical care. All counseling includes the provision of pre-test information sessions conducted with groups, couples, or individuals, the HIV test itself, and post-test counseling. The standard of care also involves the promotion of HTS through flyers in clinics and the service is offered free of charge during office hours, predominantly on weekdays.

#### Quality assurance of HTS

Rapid, on-site HIV testing has the potential to be a useful and advantageous testing strategy in community-based or outreach settings. The intervention performs HIV testing according to the South African national rapid testing algorithms with ongoing external quality assessment (EQA). All staff are fully trained in performing the rapid testing algorithm. CD4 counts are done by POC tests with ongoing EQA. VL testing are done at a laboratory with EQA participation. Training in rapid testing technology was done as part of the 10-day counseling course for counselors.

In addition to covering all of the didactic portions of the counseling and testing process, counselors practice using the test kits themselves with known HIV-positive and HIV-negative sera to ensure that they are performing and reading the tests correctly. Counselors also practiced with mock patients under the supervision of the Counselor Supervisor. Supervisors periodically observe counselors in the HTS process, using a standardized checklist, to ensure that all parts of the procedure are being followed. Counselors are recertified bi-annually with panels of HIV-positive and HIV-negative sera. They are expected to achieve 100% correct results; if they fail to do so, the counselor is taken out of the study, retrained and recertified, and monitored closely to ensure correct adherence to testing protocols. We also conduct daily test kit validation to ensure quality test results. For each mobile unit, we conduct a known positive and known negative validation. We expect perfect concordance of results. If we do not achieve this, the batch is identified and set aside. A new batch of test kits will be validated and used for further testing.

#### Personalized linkage to care (Component 3)

In this third component of the intervention, HIV-positive men are randomized into two arms: (1) standard of care HIV follow-up; or (2) POC CD4 testing with male-centered PLC.

#### POC CD4 testing with male-centered PLC

HIV-positive participants randomized into the PLC phase of the study receive POC CD4 testing. The study nurse conducts same-day CD4 testing by taking a small blood sample obtained from the participant’s fingertip by a lancet. The date of the HIV and CD4 test and symptoms reported by the participant are provided in a one-page letter to the clinic to facilitate ART initiation. At the end of the counseling session, the nurse counselor schedules a follow-up visit for the participant and their study assigned PLC clinic-based champion (CBC). The CBC coordinates schedules with the participant and visits the HIV clinic with the participant within two weeks of enrolment. PLC services are tailored for individual clients and include pro-active case-management counseling to discuss and reduce barriers to linkage to care, adherence, and the importance of disclosure. It also comprises CBC accompaniment of the participant to help them navigate the health systems and extended hours access to the ART clinic.

#### Accompaniment to the HIV clinic by the clinic-based champion

The PLC CBC discusses with the participant the usual means of travel to the clinic and encourages the participant to attend the clinic. As appropriate, the CBC may travel with the participant to the clinic by public transport or meet the participant at the clinic. At the clinic accompaniment visit, CBCs answer questions and provide support for HIV care. If several accompaniment visits are required before linking to care, the CBC may make these visits with the participant.

#### Extended clinic hours for men (happy hour)

The PLC team leader negotiates with health services to ensure that extended hours of operation for obtaining ART and services are made available to PLC participants who have conflicting engagements during regular HIV clinic hours. This service (called happy hour) is already provided to young people by the Department of Health. A sample of clinics are opened once a week during 17:00 to 20:00, especially to cater for men. This male-only HIV service allows the PLC participants to feel more comfortable in accessing services and discussing their questions and concerns more freely with the staff at the after-hours HIV clinic. The after-hours HIV clinic will offer all services normally available at a standard HIC clinic during regular work hours including HIV testing, counseling, and ART medicines.

#### Regular follow-ups by the clinic-based champion

Further follow-up visits may be scheduled for three and six months after the initial visit, if the participant has not established care at an HIV clinic. At the follow-up visits, CBCs answer questions about barriers to care and difficulties with adherence as well as provide support for HIV care. Participants complete a questionnaire on their experience accessing care, including barriers to care, risk behavior, HIV clinical care, and knowledge of HIV treatment and prevention. Examination of HIV care documentation (e.g. registration card from HIV care clinic) and recording of medications (e.g. HIV care medications and ART) takes place.

CBCs also link men to appropriate referrals and support, including arranging opportunities for men to come together for support groups with other men to talk about and discuss issues of disclosure, adherence, and retention in care.

#### HIV standard of care

HIV-positive men randomized into the standard of care arm are referred to the study counselor. All participants who get assigned to standard of care receive the HIV and NCDs testing results slip that is used as a referral letter with all testing outcomes written on it. The lay counselor provides information about HIV treatment and encourages the participant to visit the nearest clinic or any healthcare service of their choice for further clinical attention. Participants get information about being contacted by telephone at three and six months in preparation for the nine-month follow-up visit. The telephone contact at three and six months is for tracking purposes to maintain contact with the participant. At nine months, the participant is invited to participate in another short survey and DBS specimen collection. Another consent process with the participant is solicited at this point.

### Study outcomes

Aim 1: Outcome measures compare men-centered mobilization and testing strategies in intervention communities to those in control communities.

#### Primary outcomes

Proportion of men getting tested for HIV in the last 12 months. This is to find out how many men have been tested for HIV in the last 12 months.

#### Measurement of Aim 1 outcomes

Conduct post-intervention assessments in intervention and control communities (n = 1600, 8 communities × 200).
Post-intervention random survey data (focusing on self-reported testing history, other wellness-related data, health-seeking indicators, etc.); and specimen samples from men living in the study communities. We will be able to look at reported HIV status versus actual status.

Aim 2: Outcome measures compare enrolled participants assigned to PLC to those in standard care during the intervention.

#### Primary outcomes

Proportion of men linked to care for first clinic visit in the last nine months. This is to establish how many enrolled men accessed healthcare during the intervention.Proportion who remained in care in the last nine months. This is to establish how many enrolled men completed scheduled clinic visits during the intervention.Proportion with undetectable VL at exit. This establishes how many enrolled men have suppressed VL at exit.

#### Measurement of Aim 2 outcomes

This uses information collected at the nine-month exit interview.
We will conduct facility level chart abstraction to confirm linkage to care for those enrolled in the study and laboratory DBS VL assessment to establish viral suppression.

### Theoretical rationale

Our combination prevention intervention is informed by the social-ecological framework which demonstrates how effective intervention can effectively address individual, socio-cultural, and program or health facility factors that influence individual health decisions. At the individual level, men’s testing and treatment decisions require careful balancing of perceived benefits against constraints of adopting these health behaviors. Men report testing decisions as comprising a struggle between fears of the consequences of not testing (illness and death) and fears of the consequences of HIV testing (stigma and loss of status as a man). For men, there may also be fears that testing exposes their hidden sexual activities [1, 2]. Socio-cultural factors affect men’s decisions regarding healthcare [16]. Prevalent gender norms are important determinants of both decisions to undergo HTC for men and of subsequent progression through the HIV care pathway.

Social networks create powerful conduits for both support and discouragement for men on this pathway. The influences of other men in the social network regarding testing and treatment and how this feeds into ideas of masculinity as well as the influence of sexual partners, family members, and friends also factor into men’s decisions regarding testing and treatment. Health facility factors also shape the individual’s cost-benefit analysis of seeking and sustaining testing and treatment. The distance to medical services, financial and opportunity costs of travel, and the quality of care, such as waiting time and the attitude of providers, are all important factors in testing uptake and treatment compliance for men. Men thus formulate personal options and behavioral intentions while negotiating the social environment and the parameters of testing and treatment programs and they do so against a broader structural environment that in much of sub-Saharan Africa includes entrenched poverty, food security, and weakened health systems [76]. Our multi-level intervention attempts to address all three levels that affect men’s decision-making regarding testing and engagement in care.

### Data management and adverse event reporting

The assessments in the study are administered using electronic mobile data capture. The mobile data collection platform allows for offline data collection. Collected data are uploaded to the server once the network connection is re-established. Checks are placed to ensure correct information has been entered. Data from laboratory testing (i.e. plasma HIV VL) is collected by participant ID number and merged into the database. Information from the questionnaires collected via the mobile phone is uploaded to a secured server. The de facto standard for securing network traffic is Secure Sockets Layering (SSL). This technology is fully supported by the handsets used in this study and ensures that all data transferred between the device and the server is encrypted.

Similarly, when reviewing, exporting, or managing data, all communications between the browser and server are encrypted. All data are encrypted. Servers are secured by firewalls to prevent unauthorized access and denial of service attacks. Data are protected from virus threats using antivirus technology. The study database is backed up regularly. All personal identifying data will be destroyed five years after the study is completed, in compliance with the regulatory requirements of the study funder. The team is committed to ensuring that identifying data, including GPS, are secure until the time of destruction.

#### Quality assurance

To assure data accuracy and completeness, the mobile data collection platform is programmed to require data submission on all data fields. Skip patterns and logic branches are programmed to ensure that valid data are collected. Range checks are programmed on key fields to ensure data consistency. Operational data are collected for cross-check, data tracing, and validation purposes. To assure data security, all hard-copy data are stored in locked cabinets in a locked office and all electronic data are password-protected and stored on a secure server in a secure facility. To ensure protocol compliance, the Project Director conducts periodic observations of study procedures (e.g. observing the informed consent process, a face-to-face interview, or HIV test counseling), conducts periodic “retraining” on key study procedures using role-plays during staff meetings, and produces a regular quality assurance report for the PI.

### Data analysis

#### Aim 1: Cluster-Randomized component

We will test the hypothesis that the community-wide proportion of men who were tested for HIV in the past year is at least by 10 percentage points (on an absolute scale) larger in communities randomized to the active intervention compared to the standard-of-care arm. The analysis will be based on testing reports provided by men included in the post-intervention assessment. Empirical proportions of tested participants will be calculated for each community and compared between the study arms by a two-sample Welch t-test. We will test the hypothesis that the difference in proportions is ≤ 0.1 against the alternative that the difference is > 0.1 at the one-sided level of 0.05.

#### Power calculations for Aim 1

We assumed 30% annual testing rates in the standard arm (similar to testing rates observed in Project ACCEPT in the community-based HTS arm in Vulindlela site) and between-community variance in testing rates 0.007 (estimated from Project ACCEPT’s Vulindlela data). Then, the sample size of four communities per arm, with 200 men sampled from each community, provides the following power for detecting intervention effects: power 0.05 for 10% difference (30% vs 40%, null hypothesis); power 0.36 for 20% difference (30% vs 50%); power 0.86 for 30% difference (30% vs 60%); and power 0.95 for 35% difference (30% vs 65%). Thus the study is powered to detect differences in testing rates that are substantially > 20% and therefore likely to be of practical significance. The power for detecting differences of ≥ 30% is large enough to be reasonably certain that such effects are not missed.

#### Aim 2: Individually Randomized component

We will test the hypothesis that the proportion of HIV-positive men who were linked to care and maintained with undetectable VL nine months after enrolment will be the same in the POC + PLC arm as in the standard-of-care arm. The analysis will be based on men who were randomized and who completed the follow-up visit. We will use asymptotic tests for log odds ratios performed at the two-sided level of 0.05. Confidence intervals will be obtained by the same method.

#### Power calculations for Aim 2

Assuming that the rates of linkage to care and undetectable VL are 33% in the standard arm and 50% in the POC + PLC arm (odds ratio 2.0), the sample size of 175 individuals per arm yields 88% power to detect the effect of POC + PLC over standard of care. Adjusting for 20% attrition yields the sample size of 220 per arm.

#### Secondary analyses for Aim 2

We will carefully investigate the effect on attrition on the primary analysis of Aim 2. We will compare the men who do and do not present for the final visit to assess potential bias in the analysis of the primary endpoint of Aim 2. We will evaluate the attrition effect by multiple imputation of missing data using baseline characteristics of the individuals. We will compare HIV-positive men identified in Aim 1 who do and do not enroll in the Aim 2 study.

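### The Aim 2 primary analysis keeps only randomized men who attend the nine-month visit, so loss that depends on both arm and outcome can bias the comparison

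*Protocol article*

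**What the plan says.** The Aim 2 data analysis section tests whether the proportion of HIV-positive men "linked to care and maintained with undetectable VL nine months after enrolment will be the same in the POC + PLC arm" as in standard of care (SOC). On method it says "We will use asymptotic tests for log odds ratios performed at the two-sided level of 0.05". It then fixes the analysis set: "The analysis will be based on men who were randomized and who completed the follow-up visit".

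The power paragraph assumes 33% against 50%, needs 175 men per arm and raises this to 220 for 20% attrition. That allowance protects the number of completers. It does not change who is analysed.

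Attrition itself is left to the secondary analyses: men who do and do not present at the final visit are compared, and "We will evaluate the attrition effect by multiple imputation of missing data using baseline characteristics of the individuals". The Aim 3 section allows the Aim 2 success rates to be adjusted for attrition if needed; the Aim 2 primary test has no such provision.

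One outcome source does not require the man to attend. Measurement of Aim 2 outcomes says: "We will conduct facility level chart abstraction to confirm linkage to care for those enrolled in the study".

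**The concern.** Restricting the primary test to attenders conditions on something that happens after randomization. This distorts the comparison under the null when loss is related to outcome and also unequal between arms. Both are plausible here. A man who has stopped engaging is less likely to be in care and suppressed. The personalized linkage to care (PLC) arm provides accompaniment, case management and adherence support, which may affect whether he comes back. A man who dies cannot complete the visit, so under the stated rule he is removed and not counted as a failure.

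The planned secondary work does not settle the matter. Comparing completers with non-completers describes the problem. Imputing from baseline characteristics cannot correct loss driven by engagement after enrolment. If the arms lose men at different rates, the headline result could be a spurious difference in either direction, or a real effect that is shrunk or inflated.

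**Working it through.** **Inputs from the protocol article:** 440 randomized, 220 per arm; 20% attrition; 33% against 50%; log odds ratio test, two-sided 0.05. **Assumed, because the article does not give them:** the split of loss between arms (kept at a 20% average) and the success rate among lost men (0% to 10%).

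**The plan's own figure.** SE² = Σ 1/[n p(1−p)]; power = Φ(|log OR|/SE − 1.96).
- 33% against 50%, 175 per arm: log OR 0.708, SE 0.221, power 89.4%.
- OR exactly 2.0 (33% against 49.6%): power 88.1%, matching the stated 88%.
- 175/0.8 = 218.75, so 219; the plan's 220 is adequate.

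The sample size is sound. The defect is the analysis set.

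**Completer rates.** With true rate p, loss a and success d among the lost, the rate among completers is (p − a·d)/(1 − a), on 220(1 − a) men.

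*No true effect, p = 33% in both arms.* Example, loss 25% SOC and 15% PLC, d = 0: SOC 0.33/0.75 = 44.0% of 165 men; PLC 0.33/0.85 = 38.8% of 187 men; log OR −0.214, SE 0.217; two-sided rejection about 17%.

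| Loss SOC/PLC | PLC − SOC, d = 0 | Rejection | PLC − SOC, d = 10% | Rejection |
|---|---|---|---|---|
| 20%/20% | 0 | 5% | 0 | 5% |
| 22%/18% | −2.1 points | 6.8% | −1.4 points | 5.9% |
| 25%/15% | −5.2 points | 17% | −3.6 points | 11% |
| 30%/10% | −10.5 points | 51% | −7.3 points | 29% |

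Reversing the split reverses the sign. In a milder case, where lost men succeed half as often as completers, 25%/15% gives OR 0.92 and about 7% rejection.

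*True effect, 33% against 50% among all randomized men.*
- Equal 20% loss, d = 0: 0.33/0.8 = 41.25% against 0.50/0.8 = 62.5%. The difference is 21.25 points, not 17, although loss is equal.
- 30% SOC/10% PLC: difference 8.4 points (d = 0) to 11.6 points (d = 10%), power 35% to 58%.
- 15% SOC/25% PLC, d = 0: OR 3.15 against a true 2.03.

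**All 220 per arm, missing counted as failure.**
- Loss of 20% unrelated to outcome: 0.8 × 33% = 26.4% against 0.8 × 50% = 40.0%; log OR 0.620, SE 0.206, power 85.4%.
- All lost men true failures: 33% against 50% on 220 per arm; SE 0.197, power 94.9%.

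**Where that rule is itself biased.** Take 33% in both arms and loss of 25%/15% unrelated to outcome: 0.75 × 33% = 24.75% against 0.85 × 33% = 28.05%. That is a spurious +3.3 points toward PLC, with 12% rejection. At 30%/10% it is +6.6 points and 35%. Completers are unbiased in these two cases.

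**The case against.** The plan does not ignore attrition. It allows for 20% loss, compares attenders with non-attenders, plans multiple imputation and permits an attrition adjustment in Aim 3. No unequal loss is documented: the splits above are assumptions, equal loss leaves type I error at 5%, and mild imbalance moves it to 6–7%. Missing-as-failure can mislead too. Charts are planned to confirm linkage, while suppression rests on the study's own blood spot, and SOC men may use any health service they choose, so chart searches could under-record them. No mortality figure is given, so the effect of deaths cannot be sized.

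All of this stands as a limit on the size of the problem and on the remedy. It does not rescue the stated rule, because the safeguards are secondary and the imputation is confined to baseline data.

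Two stronger readings are tempting. The champion section says "Further follow-up visits may be scheduled for three and six months after the initial visit, if the participant has not established care", while the SOC section says "The telephone contact at three and six months is for tracking purposes to maintain contact with the participant". A reader might infer that PLC men who fail to link are the ones kept in contact. The text does not support this. The champion visits are optional and part of the intervention, and the section on male-focused mobile HTS (Component 2) obtains consent for three- and six-month re-contact and a nine-month exit visit without distinguishing arms. A reader might also infer that only SOC men face a second consent at nine months, since only that section mentions it. Silence about PLC in a condensed article is not evidence of a difference.

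**Conclusion.** The point holds. The article states a primary analysis set that depends on behaviour after randomization, in a trial whose intervention aims to change that behaviour, and the planned checks cannot correct the result.

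The size is conditional. Under the null, bias needs loss that is both unequal and related to outcome. With 20% average loss and 0–10% success among the lost, false rejection runs from 5% (equal loss) to 29–51% (30%/10%), in either direction. With a true effect, the estimate can be distorted even at equal loss, from 17 to about 21 points. That last figure reads 33% and 50% as rates among all randomized men. It would be too strong to say that the randomized comparison is bound to be lost; the documents show a risk of uncertain size and direction.

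**What to change.** - Make all 440 men, analysed as randomized, the Aim 2 primary set, with death or no exit viral load counted as not successful.
- Use the planned chart abstraction to establish linkage whether or not the man attends the exit visit, with the same search in both arms and attention to SOC men who attend other facilities.
- Keep the completers analysis as secondary.
- Extend the imputation to include arm, contact status and chart-recorded visits, with a range of arm-specific departures from missing-at-random.
- Report these sensitivity analyses beside the primary result, and say plainly that missing-as-failure favours the arm with less loss when loss is unrelated to outcome.
- Reconcile the sections on mobile HTS, champion follow-up and SOC about who is contacted at three and six months.

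The cost is mainly analysis wording and some further abstraction. Power is about 85% if loss is unrelated to outcome, against 89% for 33% versus 50% in 175 completers per arm, and about 95% if all lost men are failures. Some suppressed men who miss the visit will be scored as failures. Because the Blinding section says the statistician is unblinded and belongs to a team that reviews dropouts, the change should be dated and recorded before Aim 2 outcomes are compared by arm.
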